### Sample size

2.5

We plan to enroll 105 study participants (*n* = 35/group). Power is based on 27 study participants/group, allowing up to 20% attrition over the 1-year supplementation period. Preliminary data from Zn supplementation of 30 mg/day reported 58% conversion of study participants (17). We anticipate at least a 90% conversion for the 60 mg/d dose. In order to detect an increase in percent conversion from 58 to 90%, with 80% power and type I level of alpha = 0.05, 27 study participants per treatment group are required. Sample size is determined based on testing for a difference in percent conversion between the two dose groups using a one-sided Fisher’s Exact test (31).

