### Statistical analysis

2.9

This pilot study is a randomized dose-finding trial with the primary objective to establish optimal dose of Zn supplementation to achieve adequate serum Zn levels and estimate association between serum and cellular Zn levels. The effectiveness will be assessed based on the ability to increase serum Zn levels to adequate levels in the majority of participants (>90%) and in the shortest duration of supplementation and at the same time results in <10% of moderate or severe adverse events. Subjects will be deemed Zn adequate on the first occasion where their Zn serum level reaches ≥70 μg/dL. Subjects will not be included in the calculation of this proportion if they discontinue supplementation before reaching Zn-adequate status. Pearson correlation will be estimated between serum and cellular Zn levels. Violations of linearity will be assessed graphically, and sample product moment correlation method (34) will be used to produce two-sided confidence intervals for the estimated correlation. Analysis among dose groups will follow an intention-to-treat approach. Comparison of proportion of Zn adequate between dose groups will be tested using Fisher’s exact test with risk ratios at each time point. Continuous outcomes that have repeated measures taken at baseline, 4, 8, and 12 months will be analyzed with mixed effects linear regression which considers within-subject correlation of outcomes. We will assume linear time trends and test the dose effect by the treatment by time interaction term. Assumptions of normality and homoscedasticity will be evaluated in these models and appropriate variable transformations will be applied if needed. Age, sex, and NH site will be included in the models as covariates. A significance level of 0.05 will be used for each secondary outcome. To control for multiple testing across groups, the type I error will be reserved for the comparison between the placebo group and the selected Zn dose group. Summary statistics on any missing data will be reported, including types and patterns of missingness. Subjects with partial outcomes over time can be included in the model fit since the mixed-effects linear modeling framework allows inclusion of subjects having different numbers of repeated measures. Multiple imputation based on the multivariate normal model will be used in the case of missing covariates. Analysis will be performed using SAS (version 9.4; SAS Institute, Cary, NC).

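### For the 60 v 30 mg/d comparison, an unconditional exact test in place of Fisher's gives 86% power instead of 81% with the same participants; Section 2.9 should also carry over the one-sided direction set in 2.5

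*Protocol article*

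**What the plan says.** Section 2.5 (Sample size) takes 58% conversion for 30 mg/d from preliminary data and assumes a higher rate for the other dose: "We anticipate at least a 90% conversion for the 60 mg/d dose". It states that "with 80% power and type I level of alpha = 0.05, 27 study participants per treatment group are required", and that the test behind this is "testing for a difference in percent conversion between the two dose groups using a one-sided Fisher’s Exact test". Enrolment is 35 per group, "allowing up to 20% attrition over the 1-year supplementation period".

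Section 2.9 (Statistical analysis) returns to the same comparison: "Comparison of proportion of Zn adequate between dose groups will be tested using Fisher’s exact test with risk ratios at each time point". That sentence gives neither a direction nor a significance level. Neither section explains why a one-sided test at the full 0.05 was chosen.

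**The concern.** Conversion under 60 v 30 mg/d is the only comparison for which the article gives a power calculation. Two features of the test affect that power.

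- **Discreteness.** Fisher's test conditions on the total number of converters. With fewer than 30 per group few p-values are attainable, so its real error rate lies well below the nominal level and power is lost for no gain in validity.
- **Direction.** The stated power needs a one-sided test, and the section that governs the analysis does not carry that word over. An analyst working from 2.9 alone could run the test two-sided.

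At stake is the chance of missing the assumed difference. It is about 19% as planned, about 14% with a less conservative exact test at the same one-sided level, and about 31% if Fisher's test is run two-sided.

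**Working it through.** **Inputs (Section 2.5).** Conversion 0.58 (30 mg/d) and 0.90 (60 mg/d); alpha 0.05; 27 evaluable per group; 35 enrolled per group. Note that 35 × 0.80 = 28, while 27 of 35 is a loss of 8/35 = 22.9%.

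**Formulas.** Let X be the number of converters on 30 mg/d, Y the number on 60 mg/d, and n the number per group.

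- Fisher one-sided p-value for (x, y): P(Y ≥ y | X + Y = x + y), from the hypergeometric distribution. The two-sided version sums all tables with the same total that are no more probable than the one observed.
- Power = Σ Bin(x; n, 0.58) × Bin(y; n, 0.90) over the tables (x, y) that the test rejects.
- Maximum error = the largest value, over a common rate π, of Σ Bin(x; n, π) × Bin(y; n, π) over the same tables.
- Boschloo's test orders the tables by the Fisher p-value and rejects those with p ≤ c, where c is the largest cut-off for which the maximum error stays at or below 0.05. The maximum was searched over a fine grid of π from near 0 to near 1.

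**Step 1: reproduce the plan's figure.** One-sided Fisher at 0.05 gives 79.8% at n = 26 and 81.3% at n = 27. So 27 is the number at which 80% is first passed, and the stated figure is confirmed.

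**Step 2: compare tests and directions.** Maximum true error is in brackets.

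| n per group | Fisher, one-sided 0.05 | Boschloo, one-sided 0.05 | Fisher, two-sided 0.05 | Boschloo, two-sided 0.05 |
|---|---|---|---|---|
| 27 | 81.3% (3.1%) | 86.4% (4.6%) | 69.1% (2.6%) | 78.4% (4.5%) |
| 28 | 81.0% (2.9%) | 87.9% (4.7%) | 71.7% (2.8%) | 80.3% (4.6%) |

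An unconditional test based on the pooled z statistic (Barnard type) agrees closely: 86.0% one-sided and 78.4% two-sided at n = 27; 87.3% and 80.3% at n = 28.

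**Step 3: the gain.**

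- One-sided at n = 27: 86.4 − 81.3 = 5.1 points.
- Two-sided at n = 27: 78.4 − 69.1 = 9.3 points.
- Going from one-sided to two-sided Fisher at n = 27 costs 81.3 − 69.1 = 12.2 points, so the unconditional test wins back about 9 of those 12.

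**Step 4: why Boschloo cannot do worse.** At n = 27 its cut-off on the one-sided Fisher p-value is c = 0.074 instead of 0.05, so every table that Fisher's test rejects is also rejected. For example, 17/27 v 23/27 has a one-sided Fisher p-value of 0.059. Fisher's test does not reject; Boschloo's does, with error still controlled below 5%.

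**Step 5: discreteness made visible.** One-sided Fisher power falls from 81.3% to 81.0% when one participant per group is added to 27.

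**The case against.** The strongest reply is that nothing in the plan is wrong. Section 2.5 names the test, direction, level, rates and number, and the result reproduces. Fisher's test is valid and customary at this size, and its conservatism is a known property. At the plan's own specification the 80% target is already met. All of that stands, and the point is about a better choice of test, not an error.

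Three stronger readings are tempting, and the document does not support them.

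- **That 2.9 contradicts 2.5 by planning a two-sided test.** It does not say so. The two-sided intervals in 2.9 belong to the correlation between serum and cellular zinc, and the 0.05 in 2.9 is tied to secondary outcomes, whereas conversion is primary. The only level given for this test is in 2.5, beside the word one-sided. The 69% therefore describes a reading that 2.9 leaves open, not one that it states. A condensed article may also leave the direction to a fuller document.
- **That the plan falls short of its power in general.** The figures are for 27 or 28 evaluable per group. With all 35 evaluable, two-sided Fisher has 83.2%.
- **That an unconditional test restores 80% at two-sided 0.05 with 27 per group.** It gives 78.4% there and passes 80% only at 28, with little margin. If the 30 mg/d rate were 60% instead of 58%, it would be 75.6% at 28.

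It is also true that the dose is chosen by thresholds (more than 90% adequate, fewer than 10% with moderate or severe side effects; Sections 2.1 and 2.9), not by this p-value. That limits the consequence. The comparison is still the one on which the trial's size rests.

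**Conclusion.** The sample size in 2.5 is correct as disclosed. What holds is that Fisher's test uses at most 3.1 of the 5 percentage points of one-sided error that the plan allows, and that an unconditional exact test turns the unused part into about 5 points of power (81% to 86%) with the same participants and error still held below 5%. Under a two-sided test the gain would be about 9 points (69% to 78%). Separately, the direction belongs in 2.9, because the stated power depends on it.

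This rests on the plan's own rates of 58% and 90%, equal groups of 27 or 28 evaluable participants, and a single comparison at level 0.05. Other rates would change the power figures. They would not change the fact that Boschloo's test rejects whenever Fisher's does.

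**What to change.** 1. In Section 2.9, before unblinding, name an unconditional exact test (for example Boschloo's) for the 60 v 30 mg/d conversion comparison, calculated at the evaluable group sizes actually observed. State the same direction and level as in 2.5. Keep Fisher's exact test as a sensitivity analysis.
2. In Section 2.5, restate the power to match: 86% at 27 evaluable per group for one-sided 0.05. If the sponsor prefers two-sided 0.05, write 78% at 27 per group, or 80% at the 28 that remain when 35 lose 20%.
3. If Fisher's test is kept as the main test, add its direction to 2.9. Should that be two-sided, give the power as 69% at 27 per group or 72% at 28.

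The cost is two sentences, with no extra participants or data. The downside is a test that readers know less well. The sponsor should also confirm that its software (2.9 names SAS 9.4) or a checked program computes it. The threshold-based dose selection rule stays as it is.

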### Recruitment

2.6

A total of 105 residents will be enrolled from an estimated 900 elderly NH residents (Figure 1). We have support from 16 NHs (~1,600 residents) located within 1 h driving distance from Boston. Based on our previous experience (23, 32) we estimate that 900 NH residents need to be screened to identify 350 (Figure 1), who will meet our eligibility criteria (Table 2) who will then be screened for Zn and albumin levels to identify 105 subjects with low serum Zn levels. Although individual NH populations are heterogeneous, when similar methods for collection of information and time intervals are used, the comparative incidence of RI and PNA is quite similar. Our data also demonstrated (17) similar prevalence of low Zn levels in all NHs we studied in the Boston area, regardless of socioeconomic status, ethnicity, or NH affiliation (academic or not, or VA). Considerations for choosing participating NHs will include willingness to participate in the study, compliance with all state Department of Public Health regulations, number of beds (>50), compliance with state staffing requirements and sick days, and absence of shared staff between different units in multi-unit facilities (33).

### Randomization, allocation concealment, and blinding

2.7

Subjects will be assigned to each arm via block randomization with a block size of 6. The randomization will be done via the built-in random number generator included in the study database and data capture system, REDCap. Placebo and Zn supplements will be provided in identical capsules to maintain double blinding. The database manager will retain the randomization code. Other members of the study team, including the Co-PIs, will be blinded to treatment assignments. The placebo and Zn capsules have been developed to have identical appearance to ensure blinding of the treatments.

### Data collection and management

2.8

Clinical measures and study data collected on-site will be captured by the study staff using Electronic Case Report forms (eCRFs) developed in REDCap, a Research Electronic Data Capture platform hosted at the Human Nutrition Research Center on Aging at Tufts University (HNRCA) and secure study dedicated laptop. These eCRF forms are accessible via the web or an iPad app developed for use in instances where internet access is limited or lacking. In addition to standard clinical and anthropometric measures, these eCRFs will also include health status and intervention response questionnaires to assess response to intervention. REDCap is a secure HIPAA- and 21 CFR 11-compliant web-based application for building and managing online surveys and databases that are structured to support data capture for multisite clinical trials. It provides real-time data entry validation and a de-identified export mechanism to common statistical packages. Ongoing review of entered data will occur and incomplete data adjudicated within 1 week of entry. In all instances, access to the server will be restricted to data management staff at Tufts University.

Designated users from individual sites will have access for data entry, along with read access to individual site data, subject randomization, data dictionaries and collection forms. Laboratory data will be exported and be processed using Microsoft Excel and reviewed for outliers using standard statistical software (SAS). Laboratory data will be stored and archived on secure servers at the HNRCA with scheduled daily back-ups. Upon completion of the study, all data will be de-identified and converted to/archived in csv files for long-term storage and sharing. The files will contain variables with standardized naming conventions consisting of prefix, root and suffix system and include variable description labels. All data and corresponding documentation will be preserved in perpetuity and related files in the different formats will be linked by file naming conventions and revision date. Corresponding documentation including protocols, value ranges, formats and data description will be developed and stored with the data files. Adherence to the data management plan will be monitored and reviewed monthly. Implementation of the plan and progress on the data collection, archiving, and sharing will be included in reports.

### Statistical analysis

2.9

This pilot study is a randomized dose-finding trial with the primary objective to establish optimal dose of Zn supplementation to achieve adequate serum Zn levels and estimate association between serum and cellular Zn levels. The effectiveness will be assessed based on the ability to increase serum Zn levels to adequate levels in the majority of participants (>90%) and in the shortest duration of supplementation and at the same time results in <10% of moderate or severe adverse events. Subjects will be deemed Zn adequate on the first occasion where their Zn serum level reaches ≥70 μg/dL. Subjects will not be included in the calculation of this proportion if they discontinue supplementation before reaching Zn-adequate status. Pearson correlation will be estimated between serum and cellular Zn levels. Violations of linearity will be assessed graphically, and sample product moment correlation method (34) will be used to produce two-sided confidence intervals for the estimated correlation. Analysis among dose groups will follow an intention-to-treat approach. Comparison of proportion of Zn adequate between dose groups will be tested using Fisher’s exact test with risk ratios at each time point. Continuous outcomes that have repeated measures taken at baseline, 4, 8, and 12 months will be analyzed with mixed effects linear regression which considers within-subject correlation of outcomes. We will assume linear time trends and test the dose effect by the treatment by time interaction term. Assumptions of normality and homoscedasticity will be evaluated in these models and appropriate variable transformations will be applied if needed. Age, sex, and NH site will be included in the models as covariates. A significance level of 0.05 will be used for each secondary outcome. To control for multiple testing across groups, the type I error will be reserved for the comparison between the placebo group and the selected Zn dose group. Summary statistics on any missing data will be reported, including types and patterns of missingness. Subjects with partial outcomes over time can be included in the model fit since the mixed-effects linear modeling framework allows inclusion of subjects having different numbers of repeated measures. Multiple imputation based on the multivariate normal model will be used in the case of missing covariates. Analysis will be performed using SAS (version 9.4; SAS Institute, Cary, NC).

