### Design

2.1

We are conducting a one-year long RCT to determine an effective and safe Zn supplementation dosage for elderly NH residents with low serum Zn levels (< 70 μg/dL), this threshold is recommended by Institute of Medicine, Panel on micronutrients (21) and others (22). Two Zn dosages, 30 or 60 mg/d, will be tested. The primary objectives are to establish the optimal dose of Zn supplementation required to achieve adequate serum Zn levels and estimate the correlation between serum and intracellular labile Zn levels. The secondary objectives are to assess adverse events and immune outcomes and collect data on PNA to design a larger clinical trial effectively. The selection of the dose will be determined by the combination of time and dosage that exceeds threshold for achieving adequate serum Zn levels in the majority of subjects (>90%) while remains below designated threshold for incidence of the side effects (<10% moderate or severe side effects, see below).

A total of 105 male and female elderly subjects (≥65 y) with low serum Zn (<70 μg/dL) will be enrolled from a NH within 1 h driving distance from Boston (from an estimated 16 NHs, ~900 residents) and be assigned to one of the 3 groups. Group 1 will serve as control and will receive a capsule containing ½ Recommended Dietary Allowance (RDA) of all the essential micronutrients (MN), including 5 mg of elemental Zn (1/2 RDA MN); group 2 will receive a capsule containing ½ RDA MN including 30 mg/d elemental Zn, and group 3 will receive a capsule containing ½ RDA MN including 60 mg/d elemental Zn. Zn is provided as Zn gluconate. The overall study design and number of subjects is shown in Figure 1 and the frequency of data collection is shown in Table 1.

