Clinical chemistry profile, albumin, Cu, Fe, Ferritin, CRP, and complete blood count with differential measures (CBC-diff) will be analyzed on all subjects as previously described in our Zn supplementation study (17, 18). Importantly, intestinal absorption of Cu is inhibited by Zn. Thus, chronic intake of high doses of Zn may be associated with Cu deficiency (28). This concern is the main basis for the upper tolerable limit (UL) for Zn (21). However, notably, this UL refers to chronic intake of Zn in subjects with adequate Zn level and does not preclude the use of higher doses of Zn for treatment of deficiency or diarrhea. The presence of 0.8 mg Cu in our placebo and Zn capsules will ensure no adverse effect on Cu status. Further, no serious adverse effects have been reported for long-term (up to 5 yrs) intake of up to 80 mg of Zn/day in older adults (29), who had baseline serum levels higher than those proposed in this study. Blood will be examined with a Baker 9,000 Hematology Analyzer for RBC and WBC counts and a blood smear will be used to estimate WBC differentials. This information will be used for statistical adjustment by analysis of co-variance and/or for assessment of side effects. CRP is included as it is a marker of inflammation which may impact Zn levels transiently and will be used for statistical adjustments as needed. BMI will be calculated from baseline weight and standing or knee height (in subjects who cannot stand or are contracted) (30).

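### Adequacy is fixed at the first serum Zn of 70 μg/dL or more with no need to persist, so the month 8 and 12 proportions read as cumulative, although the >90% shortest-duration rule needs adequacy at a given time

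*Protocol article*

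**What the plan says.** Statistical analysis (2.9) defines the endpoint: "Subjects will be deemed Zn adequate on the first occasion where their Zn serum level reaches" 70 μg/dL or more. It adds: "Subjects will not be included in the calculation of this proportion if they discontinue supplementation before reaching Zn-adequate status". By implication, a participant who stops after a first adequate value stays in the proportion as a success.

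The readings come from "repeated measures taken at baseline, 4, 8, and 12 months", so there are three after baseline. Recruitment (2.6) describes entry on the same variable: residents are "screened for Zn and albumin levels to identify 105 subjects with low serum Zn levels", and Design (2.1) sets the limit at below 70 μg/dL.

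The proportion drives dose selection. Effectiveness means adequate levels in "the majority of participants (>90%) and in the shortest duration of supplementation", with moderate or severe adverse events below 10%. Design (2.1) states the same >90% criterion for a combination of time and dosage. Dose groups are compared by Fisher's "exact test with risk ratios at each time point".

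The rationale for the capsules (3.1) says that the design will show whether a longer period on 30 mg/d improves Zn status in most residents. Secondary outcomes (2.4.2) calls CRP a "marker of inflammation which may impact Zn levels transiently".

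**The concern.** A status awarded at the first qualifying value and never withdrawn gives a proportion that cannot fall between visits. For illustration, a participant at 71 μg/dL at month 4 and 60 μg/dL at months 8 and 12 counts as adequate throughout. Even if the share of adequate participants is the same at every visit, the cumulative share grows with each extra reading.

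This bears on two stated purposes. The >90% rule asks whether a dose brings nearly everyone to an adequate level after a given duration, and an ever-adequate proportion overstates that at months 8 and 12. The question about longer use of 30 mg/d compares later visits with earlier ones, and a cumulative status shows improvement with time even when there is none. The Introduction says that the chosen dose will go into a larger efficacy trial, so the error would carry forward.

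**Working it through.** **The plan's own figure.** The only calculation in the plan that uses conversion rates is the sample size (2.5): 58% against 90%, one-sided Fisher's exact test, alpha 0.05, 80% power. Full enumeration gives power 0.798 at 26 per group and 0.813 at 27, so the stated 27 reproduces and is not in dispute here.

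**Inputs.** From the article: cut-off 70 μg/dL, three post-baseline readings, threshold >90%, 58% conversion at 30 mg/d (2.5), and 29% of residents below 70 (Introduction). Assumed: normally distributed readings, a constant visit rate p, and a common between-visit correlation ρ of 0.5 to 0.9. The article gives no within-person variance. The 80% rate is an illustration of a dose below the threshold.

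**Formula.** With z = Φ⁻¹(p), the chance of at least one adequate value in k readings is

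1 − ∫ φ(u) [Φ((−z − √ρ·u)/√(1−ρ))]^k du.

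Month 4 has k = 1, month 8 has k = 2 and month 12 has k = 3. At k = 1 the result is p for any ρ, so month 4 is not inflated.

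| Rate at each visit | ρ | By month 4 | By month 8 | By month 12 |
|---|---|---|---|---|
| 80% | 0.5 | 80% | 91% | 95% |
| 80% | 0.7 | 80% | 89% | 92% |
| 80% | 0.9 | 80% | 85% | 87% |
| 58% | 0.5 | 58% | 74% | 82% |
| 58% | 0.7 | 58% | 70% | 76% |
| 58% | 0.9 | 58% | 65% | 68% |

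These are expected proportions. An 80% dose exceeds 90% by month 8 only if ρ is below about 0.61, and by month 12 only if ρ is below about 0.80.

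**The same question in reverse.** Solving the formula at k = 3 for a cumulative 90% gives visit rates of 70%, 77% and 84% at ρ = 0.5, 0.7 and 0.9. A simulation that also models entry on a value below 70 (assumed total SD 10–14 and within-person SD 3–7 μg/dL) gives 67–85%, in agreement.

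**Regression to the mean, kept apart.** Suppose 29% lie below 70 at screening and the supplement does nothing. With single-reading reliability R, q = Φ⁻¹(0.29) and a(u) = Φ((q − √R·u)/√(1−R)), the share adequate at least once in k readings is ∫ φ(u) a(u)[1 − a(u)^k] du / 0.29. For R from 0.9 down to 0.6 this is 21–43% at one visit and 37–70% over three. The one-visit part comes from selecting on a low value and arises under any definition of adequacy. Only the further rise comes from counting first occurrences.

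**The case against.** The best defence is that first attainment is a legitimate target. Design (2.1) speaks of the dose required to achieve adequate levels, and the rule seeks the shortest duration. The article never says outright that status is kept when later values fall. It tests proportions at each time point and analyses repeated continuous outcomes by mixed model. This shows that the cumulative reading is an inference. It remains the natural one: the definition names a first occasion, and the denominator rule treats adequacy as a state once reached. The mixed model does not feed the >90% rule.

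The size is also open to challenge. No within-person variance is given. Postponing enrolment after infection, requiring albumin above 3.0 g/dL and measuring CRP all reduce acute swings. In the earlier 30 mg/d trial, those who failed to convert started at 44–60 μg/dL, which suggests that failure followed baseline closely and that the lowest reliabilities fit poorly. That evidence is only indicative, because the earlier sample's size and baseline distribution are not shown. It supports giving a range, and it leaves the direction unchanged.

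Three stronger readings are tempting and are not supported:

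- A reader might infer that one chance reading in three always settles the endpoint. That can apply only to a decision at month 12: month 4 has one reading and month 8 has two.
- A reader might blame regression to the mean on the first-occasion rule. It comes from entry on a value below 70, acts alike in all randomised arms, and remains under a visit-by-visit definition.
- A reader might take the control arm as a direct measure of background conversion. Control participants receive 5 mg/d of Zn with half the RDA of other micronutrients, so their conversion may include a supplement effect.

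**Conclusion.** The point holds as a should-fix. The written definition makes the month 8 and 12 proportions cumulative on its natural reading, while the decision rule and the duration question need adequacy at a given time. The direction is certain: an ever-adequate proportion is never below the proportion at any one of the visits it covers. The size depends on the assumed correlation. Over the range 0.5 to 0.9, a constant 80% gains 5 to 11 percentage points by month 8 and 7 to 15 by month 12, and a constant 58% gains 10 to 24 by month 12. Whether an 80% dose would wrongly pass >90% therefore cannot be settled from the article: it would at 0.5 and 0.7 by month 12, and would not at 0.9. A dose that passes at month 4 is untouched by this problem.

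**What to change.** In Statistical analysis (2.9), define a participant as Zn adequate at a visit if serum Zn is 70 μg/dL or more at that visit, separately for months 4, 8 and 12. Apply the >90% criterion to the earliest visit at which a dose meets it and does not lose it at later visits, and use that visit as the shortest duration. Keep time to first adequate value as a descriptive time-to-event summary. Report the control-arm proportion at each visit alongside as context, noting that control receives 5 mg/d of Zn and is not a pure estimate of background conversion.

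The change is one of wording and uses the blood samples already planned. Its costs are that observed adequacy will be lower, the >90% criterion will be harder to meet, and a duration chosen at month 4 or 8 is confirmed only once the later visits are in. It does not remove regression to the mean from entry on a low value, which should be acknowledged when the proportions are interpreted.

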We will screen and record NH residents every 2 weeks for the following symptoms/adverse events: (1) Minor side effects: Nausea, and bad taste. These side effects were relatively common in studies using doses well above 60 mg/day. If patients are willing to continue taking Zn despite these minor side effects, we will continue Zn supplementation. (2) Moderate side effects: Nausea, vomiting, stomach pain, diarrhea. These adverse events are extremely rare at doses of 30 and 60 mg/day. These will be designated as not acceptable, and participants will be dropped from the study. (3) Severe side effects: Flu-like symptoms (fever, chills, cough, headache), neurologic symptoms such as paresthesia, gait disturbance or photophobia. These adverse events have not been reported at doses of 30 and 60 mg/d. Participants exhibiting these adverse events will be dropped from the study. We will record the number of side effects and their duration throughout the 12-months duration of the study for both Zn doses. If treatment stops due to adverse events this event will be counted as such, and participant will be dropped from study. If at any point more than 10% of planned enrollments have experienced at least 1 moderate or severe side effect, we will close this study arm.

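### The primary Zn-adequacy proportion leaves out participants who stop before reaching adequacy, which conflicts with the declared intention-to-treat comparison and can change the >90% decision.

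*Protocol article*

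**What the plan says.** All of the following is in the Protocol article.

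- **Target.** In Statistical analysis, a dose is effective if it can "increase serum Zn levels to adequate levels in the majority of participants (>90%) and in the shortest duration of supplementation", with under 10% moderate or severe adverse events. The Design section gives the same two-part selection rule.
- **Responder.** "Subjects will be deemed Zn adequate on the first occasion where their Zn serum level reaches ≥70 μg/dL". One adequate value is enough.
- **Exclusion.** "Subjects will not be included in the calculation of this proportion if they discontinue supplementation before reaching Zn-adequate status".
- **Analysis principle.** Three sentences later: "Analysis among dose groups will follow an intention-to-treat approach".
- **Comparison.** The next sentence reads: "Comparison of proportion of Zn adequate between dose groups will be tested using Fisher’s exact test with risk ratios at each time point".
- **Stopping for side effects.** The Secondary outcomes section states: "If treatment stops due to adverse events this event will be counted as such, and participant will be dropped from study".
- **Size.** In Sample size, 35 per group are enrolled, and "Power is based on 27 study participants/group, allowing up to 20% attrition over the 1-year supplementation period".

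**The concern.** The exclusion depends on the outcome. A participant who becomes adequate and then stops remains a success. A participant who stops while still deficient leaves the denominator and counts nowhere. That removes randomised participants because of what happened after randomisation, which is not intention-to-treat, and the intention-to-treat sentence directly precedes the test of this proportion.

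Stopping can also be a consequence of the dose, because moderate or severe side effects lead to removal from the study. Table 1 has no blood draw between baseline and month 4, so anyone removed before month 4 has no chance to be recorded as adequate.

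The proportion is the efficacy half of the dose-selection rule, and the Introduction says that the selected dose goes into the larger trial. Which of the two rules is applied can therefore settle which dose is carried forward.

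**Working it through.** **1. The plan's own figure.** Inputs (Sample size): 58% against 90% conversion, one-sided Fisher's exact test, alpha 0.05, power 80%. Full enumeration of the exact test gives 79.8% power at 26 per group and 81.3% at 27. So 27 is reproduced as the smallest group size that reaches 80%. With 35 enrolled and 20% attrition, 35 × 0.80 = 28 remain, which covers 27. The sample size has no arithmetic error.

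Its basis matters, though. The Introduction gives the 42% who did not become adequate as a share of those who completed the earlier trial, so 58% is a completer rate and 27 is a count of evaluable participants. The sample size matches the exclusion rule and does not match intention-to-treat.

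**2. Effect on the >90% decision.** Let n = 35 be randomised to an arm, d stop before adequacy, and x become adequate. The plan's proportion is x/(n − d). With all randomised counted it is x/n. Since n − d ≤ n, the first is never below the second. For each d, take the smallest x that passes >90% under the plan's rule:

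| Early stops d | Plan's rule | All randomised |
|---|---|---|
| 0 | 32/35 = 91.4% | 32/35 = 91.4% |
| 1 | 31/34 = 91.2% | 31/35 = 88.6% |
| 3 | 29/32 = 90.6% | 29/35 = 82.9% |
| 4 | 28/31 = 90.3% | 28/35 = 80.0% |
| 7 | 26/28 = 92.9% | 26/35 = 74.3% |

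The row with 7 is a worst case: it places the whole 20% allowance (0.20 × 35 = 7) before adequacy.

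**3. How far the side-effect limit protects.** If the 10% closing rule is read against the 35 planned per arm, 4/35 = 11.4% closes the arm and 3/35 = 8.6% does not. Three side-effect stops are thus compatible with selection, and three are enough for the 90.6% against 82.9% contrast. Stops for minor effects, refusal or other reasons are not capped.

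**4. Between-dose comparison, on assumed rates.** Suppose both doses succeed in 70% of all randomised, with early discontinuation of 5% at 30 mg/d and 20% at 60 mg/d. Under the exclusion the rates become 0.70/0.95 = 73.7% and 0.70/0.80 = 87.5%, with denominators of about 33 and 28. The one-sided Fisher test then favours 60 mg/d in 27.9% of trials, against 2.8% with all 35 counted in each arm. With 75% success and 0% against 20% discontinuation, the figures are 51.2% and 2.8%.

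**5. Power if all randomised are counted.** Multiply the planning rates by one minus the early attrition, assumed equal in both arms, with 35 per arm:

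| Early attrition | 30 mg/d | 60 mg/d | Power |
|---|---|---|---|
| 0% | 58.0% | 90.0% | 90.1% |
| 10% | 0.58 × 0.90 = 52.2% | 0.90 × 0.90 = 81.0% | 76.4% |
| 20% | 0.58 × 0.80 = 46.4% | 0.90 × 0.80 = 72.0% | 64.7% |

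In the last row, about 53 per arm would be needed for 80%.

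**The case against.** The strongest defence is that the plan wants the response of people who actually take the supplement. That is a defensible quantity in a dose-finding pilot, and the completer-based 58% and the evaluable 27 per group fit it. This stands as a reason to keep the proportion as a supplementary analysis. It does not reconcile the proportion with the intention-to-treat sentence.

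Three stronger readings are tempting and are not supported:

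- **That the 60 mg/d arm will lose more participants.** Secondary outcomes describes moderate side effects as very unusual at both doses and severe ones as unreported, and no discontinuation rate by arm is given. The rates in step 4 of the working are assumptions.
- **That stopping can only inflate the result.** This holds only relative to counting early stoppers as not adequate. Against what full follow-up would have shown, it can go the other way. If 32/35 = 91.4% would have become adequate and four of those stop early for unrelated reasons, the plan's rule gives 28/31 = 90.3%.
- **That a poorly tolerated dose is simply turned into an effective one.** Side effects are counted separately, the selection rule also requires under 10% moderate or severe events, and an arm can be closed. These safeguards are real but partial.

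The worst case with 7 stops should also be read as such. The 20% is an upper allowance over the whole year, participants adequate by month 4 are never excluded, and Design reports that in the earlier nursing-home study 98% took the capsule for more than 90% of the year.

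**Conclusion.** The point holds in this form: one section sets two incompatible rules for the same primary proportion, and the choice between them can reverse the >90% decision. One early stop can be enough (31/34 = 91.2% against 31/35 = 88.6%). Three early stops can move the figure from 82.9% to 90.6%, and the worst case moves it from 74.3% to 92.9%. These contrasts rest on 35 per arm and on counting early stoppers as not adequate as the reference.

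Bias in the between-dose comparison is conditional on unequal early stopping, which the documents neither state nor exclude. The contradiction and the effect on the threshold do not need that assumption.

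**What to change.** **Primary proportion.** Replace the exclusion sentence with wording such as: *All randomised participants are included in the denominator of their assigned arm. A participant who discontinues without an observed serum Zn of 70 μg/dL or more is counted as not adequate.* State beforehand how death or transfer unrelated to treatment is handled. Losses of this kind are foreseeable, since eligibility requires a life expectancy of only more than 6 months in a 12-month trial.

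**Supplementary.** Keep the present on-supplement proportion under that name, and report reasons for discontinuation by arm.

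**Data after stopping.** Reconcile the Secondary outcomes wording on removal from the study with intention-to-treat, by separating stopping the capsule from leaving follow-up. Keep the scheduled month 4, 8 and 12 data for those who stop and agree. This concerns data collection only and leaves untouched when treatment stops.

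**Cost.** No new visit types are needed, but the change goes beyond wording. Observed proportions will be lower and the target harder to reach: four early stops for any reason cap an arm at 31/35 = 88.6%, below 90% whatever the dose does, unless the death and transfer rule provides otherwise. The >90% criterion should be reviewed with that in mind. Power should be restated on the all-randomised basis, because the present 81.3% at 27 per group rests on completer rates.
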